### Randomization

2.4

Randomization will be conducted using an online computer algorithm to allocate the radical hysterectomy (RH) approach at a ratio of 2:1:1 (laparoscopy vs. laparotomy vs. gasless laparoscopy group). The computer algorithm will generate a unique code for each participant and collect basic information in addition to group assignment. Patients and study surgeons will be aware of the treatment assignment.

### Qualification requirements for the chief surgeon

2.5

The chief surgeons are carefully selected from each participating hospital and had expertise in cervical cancer surgeries. They must have performed a minimum of 50 surgeries for both LRH and ARH, with documented case histories. Each surgeon is required to submit unedited surgical videos (1 ARH and 1 LRH) for the principal investigator and the surgical quality control team to review to ensure precise surgical resection and tumor-free management.

### Treatments

2.6

For the gasless LRH procedure, a combination of special surgical instruments (**Figure 2**) and conventional laparoscopic instruments was utilized. The process involved the following steps: After inducing anesthesia, the patient was positioned in a lithotomy position, and a sterilized stainless-steel scaffold with a lifting arm was attached to the operating table. Two sterilized needles were inserted through the subcutaneous tissue of the left and right abdomen to lift the abdominal wall and provide pelvic exposure. A 2 cm mini-laparotomy incision was made, and a small Alexis wound protector was used to facilitate smooth entry of the 10 mm laparoscope. The patient was adjusted to approximately 30° in the Trendelenburg position. Four 5 mm conventional laparoscopic access ports were inserted: one at McBurney’s point, one at the anti-McBurney point, and two fingers (3–4 cm) above the umbilicus in the left and right medio clavicular lines.

**Figure 2 f2:**
[figure not shown]
Gasless laparoscopy was performed with abdominal wall suspension.

Patients underwent different surgical approaches according to group while maintaining the same surgical scope based on tumor stage as follows:

1) Patients with IA1 (LVSI+) and stage IA2 underwent modified radical hysterectomy (type B), while IB1, IB2, and IIA1 patients underwent radical hysterectomy (type C) according to the new classification of RH proposed by Querleu and Morrow (29).2) Systematic pelvic lymphadenectomy was performed, including the removal of lymph nodes adjacent to the common iliac artery, external iliac artery, internal iliac artery, and obturator fossa. Para-aortic lymph node dissection was performed where necessary, and after dissection on one side, the lymph nodes were bagged and sealed separately.3) A strict adherence to the tumor-free principle was followed, where the vagina was closed before severing it. This could be accomplished through the closure of the vagina with an obturator, forceps, a ligature ring, and transvaginal sutures during laparoscopic surgery or using an open surgical kidney pedicle during open surgery. The use of any type of uterine manipulator was strictly prohibited during the surgery.4) The ovaries may be preserved or removed depending on the patient’s condition. For patients who are younger than 45 years old, without signs of ovarian metastasis from both preoperative imaging examination and intraoperative findings, ovarian preservation will be considered. If the ovaries are preserved, ovarian transposition is recommended to avoid potential damage from subsequent radiotherapy.

Patients with high-risk factors, such as positive resection margins, lymph node metastasis, and parametrial involvement, are expected to receive adjuvant therapy. Additionally, for patients with cervical squamous cell carcinoma who meet the Sedlis criteria, adjuvant therapy is also encouraged. Postoperative adjuvant treatment will be administered in accordance with the latest NCCN guidelines.

Standardized postoperative follow-up will be strictly conducted based on the NCCN guideline, with visits scheduled every 3 months for 2 years, every 6 months for the following 3 years, and annually thereafter (**Table S1**). Routine follow-up items will include physical examinations, HPV tests, LCT, ultrasound, enhanced pelvic MRI, PET-CT, and colposcopy when deemed necessary. Moreover, detailed information on complications arising from both surgeries and adjuvant therapy will also be collected during the follow-up period.

## Statistical analysis

3

### Sample size

3.1

The primary objective of this study was to compare oncologic outcomes among patients undergoing gasless LRH, ARH, and conventional LRH, focusing on 2-year disease-free survival (DFS) as the primary endpoint. Based on previous research results, the estimated 2-year DFS rates for patients undergoing gasless LRH, ARH, and LRH were 97%, 98%, and 96%, respectively. For the study, the noninferiority margin was set at 9%, and there will be a follow-up period of 2 years.

Considering the relative complexity of performing gasless LRH in participant centers compared to leading centers, the sample ratio was set at 2:1:1 (laparoscopy vs. laparotomy vs. gasless laparoscopy group) for statistical analysis, using a one-sided test with a significance level (α) of 0.025. Additionally, a 10% dropout rate, including those lost to follow-up, was assumed for the study. Based on these considerations, the study is estimated to have a statistical power of 97% to detect any survival differences (one-sided test, α=0.025).

In summary, considering the maximum sample size, both the laparotomy group and the gasless laparoscopy group will each require 126 patients, while the laparoscopy group will require 248 patients, resulting in a total of 500 patients needed for the study.

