However, it should be acknowledged that the LACC trial also has some weaknesses (15). For instance, the survival rate of the open surgery group in the LACC trial was too high, much higher than that reported previously. Patients with recurrence were concentrated in 14 out of 33 centers, implying the presence of quality deviations among different centers in the trial. In contrast, reports from some recently published retrospective studies and meta-analyses have suggested that MIS is not inferior to open surgery for treating early-stage cervical cancer (16–19). Notably, in the subgroup analysis of the LACC trial, no survival difference was found between MIS and open surgery for patients with stage IB1 (<2 cm) (20). This finding has been corroborated by several other retrospective studies (21). Consequently, the need for additional high-quality RCTs is evident.

Certain hypotheses have been proposed to explain the poorer prognosis associated with MIS, including the use of a uterine manipulator, intracorporeal colpotomy, and the potential spillage of cells during pelvic lymphadenectomy (15). Notably, an observational study of 693 patients found that MIS with protective vaginal closure resulted in oncologic outcomes similar to those of open surgery (hazard ratio (HR): 0.63, 95% confidence interval (CI): 0.15–2.59) (21). In the Atsushi et al. study, they observed that the 3-year DFS rates (NLNT 92.4%; ARH 94.0%) and overall survival rates did not differ significantly between the MIS and open surgery groups by using the no-look no-touch (NLNT) technique, which included creation of the vaginal cuff, bagging the specimen and proceeding without an intra-uterine manipulator (22). Nevertheless, the debate regarding whether oncologic outcomes of MIS, with modifications to prevent tumor spillage, are truly equivalent to those of open surgery remains ongoing.

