#### Analysis of primary endpoints

3.3.1

Primary endpoints will be analyzed according to the intention-to-treat principle. Missing data will be censored at the last known date of patient survival. Sensitivity analysis will be performed based on the per-protocol (PP) principle. The study is intended to assess the noninferiority of the 2-year disease-free survival (DFS) rate in the LRH group compared to the ARH and gasless LRH groups, with a noninferiority limit set at 9%.

The DFS rate will be estimated using Kaplan-Meier curves, while the hazard ratio (HR) and one-sided 97.5% confidence interval (CI) will be calculated using a Cox proportional hazards regression model, confirming the proportional hazard assumption. One-sided 97.5% CIs will be reported for DFS differences and HRs, whereas other CIs will be two-sided 95% CIs unless otherwise specified.

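### A 9-point margin against an assumed 98% DFS lets conventional laparoscopy be noninferior and significantly worse at once, and the planned one-sided intervals leave out the bound that would show it

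*Protocol article*

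**What the plan says.** In the protocol article, the Sample size section gives the design rates: "the estimated 2-year DFS rates for patients undergoing gasless LRH, ARH, and LRH were 97%, 98%, and 96%, respectively". It states that "the noninferiority margin was set at 9" percentage points, "using a one-sided test with a significance level (α) of 0.025". The article gives no reason for the figure of 9. The planned arms are 248 (LRH), 126 (ARH) and 126 (gasless LRH), with 10% dropout and 97% power.

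Analysis of primary endpoints tests 2-year DFS in the LRH arm "compared to the ARH and gasless LRH groups, with a noninferiority limit set at 9" per cent. On reporting it says: "One-sided 97.5% CIs will be reported for DFS differences and HRs"; other intervals are two-sided 95% by default. The hazard ratio (HR) is a reported primary result, but no HR margin is given, and nothing says what will be concluded if LRH meets the margin while its interval excludes equality.

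Under Endpoints, a DFS event is recurrence or death from any cause.

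**The concern.** When the control arm is expected to have 2% events, an absolute margin of 9 points is large in relative terms. A margin wider than the expected confidence interval also allows the whole interval to lie between zero and the margin, on the side favouring open surgery. LRH would then be noninferior by the rule and statistically worse by the data.

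The Introduction motivates the trial by an earlier randomised trial in which minimally invasive surgery had lower DFS and overall survival. The Discussion says that the role of gasless LRH will be examined against open surgery if LRH proves to have the poorer prognosis. Readers will therefore want to know whether LRH was worse, and for 2-year DFS the reporting rule omits the bound that answers this.

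**Working it through.** **Inputs** (Sample size section): DFS 98% ARH, 97% gasless, 96% LRH; margin 0.09; one-sided alpha 0.025; 126/126/248 patients; 10% dropout, leaving about 113/113/223.

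**1. The plan's own figure.** Noninferiority of two proportions, unpooled variance, 97% power:
- Gasless vs ARH, 1:1: n = (1.960 + 1.881)² × (0.98×0.02 + 0.97×0.03) / (0.09 − 0.01)² = 14.75 × 0.0487 / 0.0064 = 112.3, so 113; 113/0.9 = 126. This matches.
- LRH vs gasless, 2:1: 112 in the gasless arm. Multiplying by 1.1 gives 124 and hence 248 LRH; dividing by 0.9 gives 125 and 250. This is in line with 248.
- LRH vs ARH at 248/126: SE = √(0.98×0.02/126 + 0.96×0.04/248) = 0.0176; power = Φ(0.07/0.0176 − 1.96) = 97.8%. After dropout (223/113) SE = 0.0186 and power is 96.5%.

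The sample size thus follows from the margin and is not in question here. The 97% is power for noninferiority.

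**2. The margin on the hazard scale.** Under proportional hazards, HR at the margin = ln(S − 0.09)/ln(S), where S is control DFS:

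| Control 2-year DFS | DFS at the margin | HR |
|---|---|---|
| 98% (assumed ARH) | 89% | 5.77 |
| 97% (assumed gasless) | 88% | 4.20 |
| 96% | 87% | 3.41 |
| 95% | 86% | 2.94 |
| 94% | 85% | 2.63 |

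The last three rows are a sensitivity range, not design assumptions. The planned LRH effect is itself ln(0.96)/ln(0.98) = 2.02.

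**3. Interval width against the margin.** At the design rates the 95% interval for LRH vs ARH is 2 × 1.96 × 0.0176 = 6.9 points wide, or 7.3 after dropout. Both are below 9, so an interval can fit wholly between 0 and 9.

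**4. Examples.**
- After dropout, 11/223 LRH vs 0/113 ARH events: excess 4.9 points, score (Miettinen-Nurminen) 95% CI 1.6 to 8.6, two-sided Fisher p = 0.018. Noninferior and significantly worse.
- A zero cell is not required. At full enrolment, 16/248 vs 2/126: excess 4.9 points, Wald 95% CI 1.1 to 8.6, Fisher p = 0.041, Farrington-Manning noninferiority z = 1.99 against 1.96. The same double result.

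**5. Frequency.** Exact binomial enumeration at 223/113 for the planned 96% vs 98%:

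| Method | Noninferior and significantly worse |
|---|---|
| Score noninferiority, Fisher p < 0.05 | 3.6% |
| Score interval for both | 6.6% |
| Wald interval for both | 22.5% |

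If LRH truly had 94% DFS (6% events, three times 2%), noninferiority would still be declared in 62% (score) to 67% (Wald) of trials.

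**The case against.** Several points on the other side stand.

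- **The HR depends on its inputs.** A reader might infer that the plan accepts a nearly six-fold hazard of recurrence. The documents do not support that as a flat statement. The 5.8 needs a true ARH rate of 98% and proportional hazards, and it concerns recurrence or death. The Introduction cites an open-surgery series with 94.0% DFS at 3 years; at a control rate of 94% the formula gives 2.6.
- **The Wald frequency misleads.** A reader might take the double result to occur in more than a fifth of trials. Of the Wald probability, 41% comes from zero ARH events, where Wald gives that arm no variance, and 91% from zero or one. The Fisher and score figures are the ones to use.
- **The one-sided interval is not the cause.** Its limit equals the corresponding two-sided 95% limit. The width of the margin creates the double result; the one-sided format only omits the other bound.
- **The result is not concealed altogether.** Kaplan-Meier estimates, the difference and the HR are all reported, and 5-year DFS and overall survival are compared by log-rank or Cox methods. None of this supplies the missing bound for 2-year DFS or a rule for interpreting it.
- **The margin's rationale may stand elsewhere.** An article condenses the full protocol, so its silence does not show that no reason exists.

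A reader might also infer that the margin should be cut to what 500 patients can support: 8.0 points for 90% power or 7.2 for 80%. Those values come from the sample size and not from clinical acceptability, and they still equate to HRs of ln(0.90)/ln(0.98) = 5.2 and ln(0.908)/ln(0.98) = 4.8. That change is not recommended.

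**Conclusion.** The point holds as one of reporting and interpretation. On the plan's own rates the margin tolerates 11% against 2% DFS events, and the expected interval of about 7 points is narrower than the margin. LRH can therefore be declared noninferior while significantly worse, in roughly 4% to 7% of trials at the planned rates. The stated intervals would not show it.

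The sizes rest on the assumed DFS rates. The HR figures also need proportional hazards. The frequencies treat 2-year DFS as a simple proportion with 10% of patients removed, whereas the plan censors them in a Kaplan-Meier analysis, so they are approximate. The sample-size arithmetic is sound for the margin chosen, and nothing here shows that the noninferiority test is invalid.

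**What to change.** In Analysis of primary endpoints:

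1. Replace the one-sided 97.5% intervals for the primary DFS differences and HRs with two-sided 95% intervals. The limit compared with 9 points, and the alpha, stay the same.
2. Add: if the interval for LRH vs ARH lies wholly between 0 and the margin on the side favouring ARH, the report will state that LRH was statistically worse by less than the margin, alongside the noninferiority result.
3. State that the noninferiority decision rests on the Kaplan-Meier difference in 2-year DFS, and give the HR equivalent of 9 points over a range of control rates, as tabulated above.

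The cost is wording only. No patients are added, power is unchanged and no noninferiority verdict is withdrawn. The sponsor accepts a less favourable description in the few trials where both results occur. Because the decision rule is untouched, the change can be made even though recruitment began in November 2020.

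### The stated 97% power is for noninferiority at the 9-point margin, not for detecting survival differences; power for the assumed 2-point and 1-point differences is roughly 20% and 7%

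*Protocol article*

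**What the plan says.** All the inputs stand in the Sample size section (3.1) of the protocol article:

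- Rates: "the estimated 2-year DFS rates for patients undergoing gasless LRH, ARH, and LRH were 97%, 98%, and 96%, respectively".
- Margin: "the noninferiority margin was set at 9%, and there will be a follow-up period of 2 years".
- Test: "using a one-sided test with a significance level (α) of 0.025".
- Allocation: "the sample ratio was set at 2:1:1 (laparoscopy vs. laparotomy vs. gasless laparoscopy group".
- Dropout: "a 10% dropout rate, including those lost to follow-up, was assumed for the study".
- Sizes: "both the laparotomy group and the gasless laparoscopy group will each require 126 patients, while the laparoscopy group will require 248 patients", 500 in total.

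From these the section concludes that "the study is estimated to have a statistical power of 97% to detect any survival differences (one-sided test, α=0.025". The sizes are introduced as the largest requirement: "considering the maximum sample size, both the laparotomy group and the gasless laparoscopy group will each require 126 patients".

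The Analysis of primary endpoints (3.3.1) sets a different kind of hypothesis from the one in the power sentence. LRH is to be shown noninferior to ARH and to gasless LRH on 2-year DFS, with a 9% limit. No difference or superiority test is given anywhere as the basis of the 97%.

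**The concern.** Power to show noninferiority and power to detect a difference answer different questions. The first is the chance of ruling out a deficit of 9 points or more when the true deficit is 1 or 2 points. The second is the chance that a true deficit of 1 or 2 points is found statistically significant. When the margin is several times the assumed difference, the first can be very high while the second is close to alpha.

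The power sentence attaches the first figure to the second question and extends it to differences of any size. A reader who takes it at its word could read a non-significant comparison of DFS as strong evidence that the approaches do not differ. The safety of laparoscopic relative to open surgery is the controversy that motivates the trial, so the distinction matters for how the result will be read.

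**Working it through.** **Inputs** (all from section 3.1). DFS at 2 years: LRH 0.96, ARH 0.98, gasless 0.97. Margin 0.09. One-sided alpha 0.025, so z = 1.96. Evaluable patients after 10% dropout: LRH 248 × 0.9 = 223.2; ARH and gasless 126 × 0.9 = 113.4 each.

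**Step 1: standard errors** of the difference in proportions, unpooled, SE = √[p₁(1−p₁)/n₁ + p₂(1−p₂)/n₂]:

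- LRH vs ARH: √(0.0384/223.2 + 0.0196/113.4) = 0.01857
- LRH vs gasless: √(0.0384/223.2 + 0.0291/113.4) = 0.02070
- Gasless vs ARH: √(0.0291/113.4 + 0.0196/113.4) = 0.02072

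**Step 2: reproduce the plan's 97%.** Noninferiority power = Φ[(0.09 − d)/SE − 1.96], where d is the assumed deficit:

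- LRH vs ARH, d = 0.02: Φ(3.769 − 1.96) = 96.5%
- LRH vs gasless, d = 0.01: Φ(3.864 − 1.96) = 97.2%
- Gasless vs ARH, d = 0.01: Φ(3.860 − 1.96) = 97.1%

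The stated figure is therefore a noninferiority power.

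**Step 3: work back to the sizes.** For 97% power, n in the smaller or comparator arm = (1.96 + 1.881)² × [p_T(1−p_T)/k + p_C(1−p_C)]/(0.09 − d)², with k the allocation ratio; then divide by 0.9 for dropout.

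- Gasless vs ARH, k = 1: 112.2, so 113 per arm; 113/0.9 gives 126. This is the stated ARH and gasless size.
- LRH vs gasless, k = 2: 111.3 gasless and 222.7 LRH, so 223 LRH; 223/0.9 gives 248. This is the stated LRH size.
- LRH vs ARH, k = 2: 116.8 ARH, so 117; 117/0.9 gives 130, with 260 LRH.

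The 126 and 248 match the first two comparisons exactly. LRH vs ARH is the most demanding of the three and falls slightly short of 97%.

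**Step 4: power to detect the assumed differences,** with the same SE, sizes and alpha. Power = Φ(d/SE − 1.96):

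- LRH vs ARH: Φ(1.077 − 1.96) = 18.9%
- LRH vs gasless: Φ(0.483 − 1.96) = 7.0%
- Gasless vs ARH: Φ(0.483 − 1.96) = 7.0%

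**Step 5: does the choice of test matter?** For LRH vs ARH the log-rank approximation uses HR = ln 0.96/ln 0.98 = 2.02 and 223.2 × 0.04 + 113.4 × 0.02 = 11.2 expected events. Power is Φ(√(11.2 × 0.337 × 0.663) × ln 2.02 − 1.96) = 19.8%. For the 1-point differences the same approximation gives 7.0% and 7.1%.

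Other tests for LRH vs ARH give about 13% (pooled z), 11.7% (pooled z, exact enumeration), 8.4% (Fisher) and 26% (Wald, exact enumeration). The range is thus about 8% to 26%. For the 1-point differences the same set of tests runs from about 2% (Fisher) to 12% (Wald, exact enumeration, LRH vs gasless).

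**The case against.** The best defence is that nothing was miscalculated. The 97% and the group sizes follow from the stated inputs, the 9-point margin stands in the same section, and section 3.3.1 states the noninferiority objective outright. A careful reader of both sections can see which hypothesis was powered. That defence stands for the design: margin, alpha, sample size and analysis are untouched. It does not rescue the sentence, which makes an explicit numerical claim about another hypothesis that the section's own inputs contradict.

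A second objection is that the difference powers depend on the test. That stands, and it is why they are given here as roughly 20% and about 7%.

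Several stronger readings are tempting, and the document does not support them:

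- *The gasless question formally hinges on first detecting an LRH-ARH difference.* The Discussion says that gasless laparoscopy will be assessed against open surgery if LRH proves worse than ARH. This is discussion prose; it defines no test, threshold or testing order.
- *The trial is too small because the maximum was missed.* The gap is 0.5 points of power, or 130 + 130 + 260 = 520 patients instead of 500, under one approximate formula. The section does not say which comparison the 97% refers to.
- *True noninferiority power is well below 97% under another interval method.* The article names no interval method for the difference, and that choice is commonly left to the analysis plan.

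**Conclusion.** The concern holds. As a statement about detecting differences, 97% is wrong by a wide margin: roughly 20% for the assumed 2-point LRH-ARH difference and about 7% for each 1-point difference. As a statement about noninferiority at 9 points it is right to within half a point (96.5% to 97.2%).

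These figures assume the stated rates, the full 10% dropout, one-sided alpha 0.025 and the normal approximation. They concern 2-year DFS only and do not carry over to the log-rank or Cox comparisons of 2-year OS and 5-year DFS/OS in section 3.3.2. It would be wrong to infer that the trial is undersized for its primary aim. The fault lies in what the power is said to be for.

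**What to change.** Replace the power sentence in section 3.1 with text along these lines:

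> Under assumed 2-year DFS rates of 96%, 98% and 97% for LRH, ARH and gasless LRH, one-sided α = 0.025 and 10% dropout, the trial has about 96-97% power (normal approximation) to show noninferiority at the 9-point margin: 96.5% for LRH vs ARH, 97.2% for LRH vs gasless LRH and 97.1% for gasless LRH vs ARH. It is not powered to detect differences of 1 to 2 points; a non-significant difference test is not evidence of no difference.

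For the sentence on group sizes, either drop the word maximum or state that 126 and 248 give 97% for the two comparisons involving gasless LRH and 96.5% for LRH vs ARH.

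The cost is a text change only. Patients, follow-up, margin and analysis stay as they are. The plan gives up a favourable-sounding claim that its inputs do not support.
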